**Methods:**

This is a prospective, unicenter, randomized, unblinded, pre- and postintervention study. The groups will be randomized (MOON vs control) via an electronic case report form. The MOON intervention will be performed 2 times per week for 10 weeks (30 minutes per session). The first 5 weeks (10 sessions) will be conducted face-to-face at the Puerta de Hierro University Hospital, and the remaining weeks will be conducted via the internet at the participants’ homes. The total sample consists of 152 patients aged between 7 and 18 years. All participants have a clinical diagnosis of ADHD under pharmacological treatment. Data collection will be used to obtain demographic and clinical data. The data will be recorded using REDCap. Measures will be made through clinical scales for parents and objective tests of cognitive functioning in patients. Additional information on academic performance will be collected. The study has a power greater than 80% to detect differences. Student *t* test, 2-factor analysis of variance (ANOVA), and Mann-Whitney analyses will be performed according to each variable’s characteristics.

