### Hypothesis

Our main hypothesis is that patients with ADHD using MOON will improve their emotional regulation more than the control group. The efficacy will be evaluated by measuring the change produced from the baseline evaluation (day 0) and the final evaluation visit (day 90), aiming for a decrease of 3 to 4 points in the global score of the Strengths and Difficulties Questionnaire (SDQ) filled by the patient’s parents.

As secondary hypotheses, the difference with the control group in measures such as ADHD core symptomatology, cognitive abilities, and academic performance will be assessed. Our secondary hypotheses are listed in Textbox 1.

Secondary hypotheses of the study.H2: Patients with Attention deficit hyperactivity disorder (ADHD) using The Secret Trail of Moon (MOON) video game will improve in core ADHD symptoms compared with the control group.H3: Patients with ADHD using MOON will improve their cognitive functioning compared to the control group.H4: Patients with ADHD using MOON will improve in academic performance with respect to the control group.H5: A change in platform (face-to-face, internet) will not entail differences in emotional regulation.H6: There will be no clinically meaningful side effects associated with the video game.

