### Analyses

#### Sample Size Calculation

Based on similar investigations with hypotheses that are centered around the administration of the SDQ [52], our sample size calculation shows the need to perform the study on approximately 152 participants with a diagnosis of ADHD to cover most of the possibilities with a Cronbach α of 0.05 and a statistical power of 80%, taking into account a 15% dropout rate. We performed the sample size calculation to contrast a mean in the control group of 11 points on the SDQ global score versus a 2-point mean drop (symptomatologic improvement) in the experimental group with a pooled SD of 4. This estimate covers other less conservative situations, such as a difference of up to 4 points.

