#### Study Population

The intention-to-treat (ITT) analysis population is defined as participants who are randomized and receive at least 10 sessions, and the per-protocol population is defined as participants who will complete 100% of the training. All analyses will be performed on the premise of the ITT analysis.

A 2-way analysis of variance (ANOVA) will be performed, with time (pre and post) and group (experimental vs control) as factors and each measure as dependent variable. The difference between the study groups will be considered significant when P<.05.

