#### Safety and Adherence Analysis

Additional measures have been taken concerning the previous clinical trial [32] to assess the occurrence of side effects. Hypothesis 6 (there will be no side effects associated with the video game) is related to this aspect. To mitigate the possibility of motion sickness due to VR use, the UKU test will be used. In the previous clinical trial, nonsignificant effects related to sleep were observed; therefore, in this clinical trial, the SDSC scale will be used to assess this symptomatology in depth. Since people with ADHD are more prone to addictive behaviors related to video games [53], two main precautions will be taken: (1) adapting the game design so as not to encourage addictive behaviors [28] and (2) collecting additional information with the GASA test.

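### H6 predicts no meaningful side effects, but the only stated rule for its sleep and gaming scales (SDSC, GASA) is a difference test at P<.05, and a non-significant result cannot support H6

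*Protocol article*

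**What the plan says.** In the Hypothesis section (Textbox 1), H6 states: "There will be no clinically meaningful side effects associated with the video game". The Safety and Adherence Analysis section repeats it without the qualifier on clinical importance: "there will be no side effects associated with the video game". That section assigns three instruments to the question: UKU for motion sickness, SDSC for sleep ("the SDSC scale will be used to assess this symptomatology in depth") and GASA for game addiction. It gives no test, threshold or margin of its own.

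Table 1 schedules SDSC and GASA at inclusion and at the final visit, with no restriction by arm. The model under Study Population is a two-way ANOVA "with time (pre and post) and group (experimental vs control) as factors and each measure as dependent variable", followed by one decision rule: "The difference between the study groups will be considered significant when P<.05". The abstract allows some choice of test, namely the Student t test, "2-factor analysis of variance (ANOVA), and Mann-Whitney analyses will be performed according to each variable’s characteristics". All of these look for a difference between groups.

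UKU is completed only by VR players, after each training session. It has no control values and no pre/post pair, so this ANOVA cannot be applied to it.

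**The concern.** H6 predicts an absence. The stated rule can count evidence against it, because a significant worsening in the MOON arm would refute it. The rule contains no outcome that counts for it, because a non-significant difference may mean no harm or too few children to see it. No size of worsening is attached to the words on clinical importance, so a result cannot be compared with a limit either.

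This matters because the device has no CE marking, is tested in children from age 7, and is discussed by the article itself in terms of sleep and addictive gaming. If the trial later reports H6 as supported on SDSC and GASA, the written rule will not have justified that statement.

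**Working it through.** **1. What the trial was sized for.** The Sample Size Calculation section uses "a 2-point mean drop (symptomatologic improvement) in the experimental group with a pooled SD of 4", alpha 0.05, 80% power and 15% dropout.
- Normal approximation: n = 2 × (1.960 + 0.842)² × (4/2)² = 62.8, so 63 per arm. The t-based value is 64.
- 64 / 0.85 = 75.3, so 76 per arm and 152 in total. The stated 152 is reproduced (two-sided test).

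The trial is therefore sized for a 0.5 SD mean difference on the SDQ. No safety measure entered the calculation.

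**2. Children analysed.** 76 × 0.85 = 64.6, about 65 per arm with both readings.

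**3. Power of the stated rule for harm in a minority.** The article gives no harm rates, so these are assumptions: a fraction f of MOON children worsens by 1 SD, the rest are unaffected, pre-post correlation r is 0.5 to 0.7, and the test is two-sided at 5%. With the SD of a single reading set to 1:
- SD of change = √(2(1 − r)): 1.00 for r = 0.5 and 0.775 for r = 0.7.
- Mean shift = f × 1 SD. The variance of change in the MOON arm rises by f(1 − f).
- For f = 10%, r = 0.5: SE = √((1 + 1.09)/65) = 0.179, 0.10/0.179 = 0.56, power about 9%.
- For f = 10%, r = 0.7: SE = √((0.60 + 0.69)/65) = 0.141, 0.10/0.141 = 0.71, power about 11%.

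Simulation (20,000 trials per setting) agrees:

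| MOON children worsening by 1 SD | Trials with P<.05 |
|---|---|
| 5% | about 6% |
| 10% | about 8% to 11% |
| 20% | about 19% to 28% |

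If 10% worsen by 2 SD, the figure is still only 17% to 25%.

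**4. Would a per-child test do better?** Count a child as worse if the change is at least 1 baseline SD.
- Background share from random variation: P(Z > 1/SD of change) = 16% (r = 0.5) or 10% (r = 0.7). An affected child exceeds the limit with probability 50%.
- With 10% affected, the MOON share is 0.159 + 0.10 × (0.50 − 0.159) = 19%, or 0.098 + 0.10 × (0.50 − 0.098) = 14%. The excess is 3 to 4 points.
- A significance test on these proportions is positive in about 8% to 11% of trials, the same as the test on means.

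Moving from means to proportions therefore gains no power.

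**5. What an interval rule would do.**
- Half-width for the excess proportion: 1.96 × √(2p(1 − p)/65) = 10 points at p = 0.10 and 13 points at p = 0.16.
- Half-width for the mean difference in change: 1.96 × SD of change × √(2/65) = 0.34 SD (r = 0.5) or 0.27 SD (r = 0.7).
- With an assumed margin of 10 points on the upper 95% limit, a no-harm claim would be allowed in about 17% to 20% of trials when 10% are harmed. By comparison, about 90% of such trials are non-significant. A harmless game would pass in about 35% to 50%.

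**The case against.** The strongest reply is that the decisive step is not in the text. A reader might infer that a non-significant SDSC or GASA result will be read as no harm, and that about nine trials in ten would then declare the game safe. No section says so. The rule states when a difference counts as significant and is silent on the opposite case. The Safety and Adherence Analysis section reports that a non-significant sleep effect in the previous trial led the authors to add the SDSC, which points the other way. This stands, so the point is limited to what the rule can support.

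A reader might also infer that all of H6 rests on the ANOVA. It does not. UKU is per-child, per-session information outside that model, although it covers only VR players and has no comparator.

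A third tempting reading is that comparing means is what hides harm in a minority. Step 4 above does not bear this out: a per-child test detects it no better.

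Finally, safety tables and thresholds may be in the full protocol or analysis plan, which are not shown. Their absence from an article is no fault, and none is claimed here. What remains is that the article attaches a difference rule, covering each measure, to a hypothesis of no harm. The t test and Mann-Whitney named in the abstract do not change this.

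**Conclusion.** The point holds for SDSC and GASA. The only decision rule the article states for them can refute H6 but cannot support it, and at this sample size non-significance carries little information: a 1 SD worsening in 10% of MOON children would go undetected in about nine trials in ten. That figure rests on assumed harm rates, about 65 children per arm with both readings, a two-sided 5% test and a pre-post correlation of 0.5 to 0.7. It describes the power of the test and does not predict what the authors will conclude. The cause is the inference rule and the sample size. As H6 is a secondary hypothesis and the remedy is one of analysis and wording, this is a change that should be made. It does not undermine the primary analysis.

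**What to change.** In the Safety and Adherence Analysis section:
- State that H6 will not be concluded from P≥.05 on SDSC or GASA.
- For each scale, report the between-arm difference with its 95% confidence interval, both for mean change from D0 to D90 and for the number and percentage of children per arm who worsen by a prespecified amount.
- Claim no clinically meaningful side effects on these scales only if the upper limit lies below a prespecified margin. Otherwise give the estimate and interval without that claim.
- Reconcile the two wordings of H6, one of which drops the qualifier on clinical importance.

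The 1 SD criterion and 10-point margin used above are illustrations. The margin should be set with the noise of the criterion in mind, because true harm in 10% of children appears as an excess of only 3 to 4 points in step 4.

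The cost is one paragraph and one table, with no new data or patients. The real downside is the wide interval, about ±10 to 13 percentage points for the excess proportion, so H6 may not be claimable on these scales even if the game is harmless.

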### Participants

#### Sample

A total of 152 patients (76 cases versus 76 controls) with a clinical diagnosis of ADHD according to the DSM-V (Diagnostic and Statistical Manual of Mental Disorders, Fifth Edition) will be enrolled. All participants will have a clinical diagnosis of ADHD, take ADHD medication, be clinically stable, and have a Clinical Global Impression (CGI) score between 3 and 6 before entering the trial. Medication will not change during the investigation unless changes are required for clinical reasons. A 15% loss rate is expected. The inclusion and exclusion criteria are summarized in Textbox 2.

Participant inclusion and exclusion criteria.Inclusion criteria:Age 7 to 17 years (may turn 18 during the study)Clinical diagnosis of attention deficit hyperactivity disorder (ADHD) in any presentationTaking pharmacological treatment for ADHDAbility to follow verbal instructionsAbility to play a video game (not necessary to play regularly)Clinically stable, with ADHD symptomatology severity based on a clinician-assessed Clinical Global Impression (CGI) score between 3 and 6Exclusion criteria:Patients with severe symptoms (> or equal to 5 CGI) or very mild symptoms (CGI < or equal to 1)Patient at risk of suicide (according to the clinical judgment of the professional in charge of the patient)Motor difficulties that prevent playing the video gameParticipation in other similar studiesIntention to initiate any psychotherapeutic treatment (including cognitive-behavioral therapy) in the next 3 months of the course of participation in the clinical trial

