#### Randomization and Masking

To warrant clinical trial randomization, a random block sequence of 76 “1” (experimental) and 76 “2” (control) in 4 blocks of 38 numbers (19 “1” and 19 “2”) will be generated using the R program (R Foundation for Statistical Computing) by author [name] [33]. The sequence will be unknown to the recruiters [34].

In the preinclusion phase, patients will be informed about the research by the principal investigator (author [name]) and their suitability will be assessed according to the inclusion and exclusion criteria (Textbox 2). Subsequently, another author ([name]) will explain the research procedure in detail and summon the prerecruited participants. Once the consent form is signed, they will be randomly assigned by blocks using the electronic CRF with a ratio of 1:1. Randomization of the groups (MOON vs control) will be performed by the electronic CRF REDCap.

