### Psychometric Assessments

#### Preinclusion

##### CGI Scale for Clinicians

Symptom severity will be measured with the CGI scale [38] (approximately 1-minute duration). ADHD symptomatology severity based on clinician-assessed CGI score (between 3 and 6) for the inclusion criteria.

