#### CGI for Parents

Symptom severity will be measured with the CGI adapted for parents (approximately 1-minute duration) consisting of a “thermometer” with a Likert scale ranging between 1 and 10 [44].

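### The upper CGI limit for entry is contradictory: scores of 5 and 6 meet both an inclusion and an exclusion criterion

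*Protocol article*

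**What the plan says.** The protocol article states the entry range for CGI severity three times:

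- **Sample, main text:** all participants are to "have a Clinical Global Impression (CGI) score between 3 and 6 before entering the trial".
- **Sample, Textbox 2, inclusion list:** the same limits, 3 and 6, tied to the clinician's rating.
- **Psychometric Assessments, CGI Scale for Clinicians:** "ADHD symptomatology severity based on clinician-assessed CGI score (between 3 and 6) for the inclusion criteria".

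The exclusion list in Textbox 2 sets a different upper limit. It removes "Patients with severe symptoms (> or equal to 5 CGI) or very mild symptoms (CGI < or equal to 1").

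Randomization and Masking says that at preinclusion, for prospective participants, "their suitability will be assessed according to the inclusion and exclusion criteria (Textbox 2"). Both lists are therefore in force at the same step. Nothing in the article says which list governs a score of 5 or 6.

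**The concern.** The clinician CGI is the only severity measure used for entry, so its limits determine how severely affected the enrolled children may be. The inclusion range runs to 6, while the exclusion starts at 5 and labels that level severe. Two readers can take different trial populations from the same textbox, one with CGI 3 to 4 and one with CGI 3 to 6.

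The stake is applicability and the reporting of deviations. A child enrolled with a score of 5 or 6 complies with one line of Textbox 2 and breaches another. Until the limit is settled, the report cannot say whether that child was eligible, or whether the findings extend to children whom the article itself calls severe.

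**Working it through.** **Inputs** (all from the protocol article)

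| Item | Rule | Place |
|---|---|---|
| Inclusion | CGI 3 to 6 | Sample, main text; Textbox 2; CGI Scale for Clinicians |
| Exclusion | CGI 5 or more, or 1 or less | Textbox 2 |
| How applied | Both lists together, at preinclusion | Randomization and Masking |

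**Step 1: overlap of the two lists.** Assume whole-number scores and that both ends of the inclusion range count.

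- Inclusion set = {3, 4, 5, 6}
- Exclusion set = {1 or less} ∪ {5 or more}
- In both = {5, 6}, which is 2 of 4 admitted scores
- In inclusion only = {3, 4}

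If the range were read without its end points, inclusion would be {4, 5} and the overlap would be {5}. The conflict remains, so it does not depend on how the end points are read.

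**Step 2: is it a different scale?** The article has a second CGI: "Symptom severity will be measured with the CGI adapted for parents", a thermometer from 1 to 10. Table 1 places it at the inclusion and final visits. At preinclusion Table 1 lists only the clinical CGI, and the inclusion criterion names the clinician's rating. The parents' scale is an outcome measure and does not explain the two limits.

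**Step 3: the lower end.** A score of 2 is not on the exclusion list, but it fails inclusion and is therefore ineligible. There is no conflict at that end.

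**Step 4: does the sample size depend on it?** The Sample Size Calculation section uses "a 2-point mean drop (symptomatologic improvement) in the experimental group with a pooled SD of 4", with 80% power and 15% dropout. The test is assumed two-sided at 0.05, since sidedness is not stated.

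- Standardised difference = 2 / 4 = 0.5
- Two-sample t-based calculation: 63.77, rounded up to 64 per arm
- Inflated for dropout: 64 / (1 − 0.15) = 75.29, rounded up to 76 per arm
- Total = 2 × 76 = 152, the plan's figure

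The normal approximation gives 63 per arm, 63 / 0.85 = 74.1, rounded up to 75 per arm and 150 in total. The stated 152 reproduces, and no CGI limit enters the formula. The article gives no SDQ data by CGI level, so any effect of the severity mix on the assumed SD of 4 cannot be calculated.

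**The case against.** The strongest reply is that the criteria can be applied as written. A child must meet every inclusion criterion and no exclusion criterion, so the two lists together yield one determinate set, CGI 3 to 4. Textbox 2 is also presented as a summary, and the article says the ethics committee and the regulator approved version 4 of the protocol, which is not shown. The overlap may have arisen in condensing.

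Part of this stands. The rules are not impossible to apply, and the operative protocol may be clean. But the article states no precedence of exclusion over inclusion. That reading would also leave the upper half of a range stated three times empty, with the limit of 6 serving no purpose. Both limits are printed in full, so this is a conflict in stated text and not detail left to another document.

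A reader might infer several stronger things that the article does not support:

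- **The whole trial population is undefined.** Age, diagnosis, medication and the other criteria are specified, and scores of 3 and 4 are clearly eligible. Only the upper severity bound is in doubt.
- **The gap at CGI 2 is a second contradiction.** Exclusion criteria need not mirror inclusion limits, and a score of 2 is simply ineligible.
- **The 62 participants enrolled by 26 September 2023 entered under the conflicting text.** Without version 4 this is not shown, and their entry scores are not given.
- **Recruiters choose a rule case by case, or children will be removed after results are seen.** The article gives the preinclusion assessment to the principal investigator at a single centre. Its analysis populations are defined by sessions received and training completed, not by eligibility.
- **The comparison between arms is biased.** Eligibility is assessed before consent and randomisation, and the sequence is concealed from recruiters, so this ambiguity does not act differently on the two arms.

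**Conclusion.** The point holds for the upper CGI limit. Scores of 5 and 6, two of the four admitted values, meet both an inclusion and an exclusion criterion, and nothing else in the article resolves it. This is an error in a stated eligibility threshold. Its consequence is for applicability (CGI 3 to 4 or CGI 3 to 6) and for deviation reporting, not for the validity of the randomised comparison or the sample size of 152.

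The count of two assumes whole-number scores with both end points included; under the strictest reading one score, 5, still conflicts. How many children are affected cannot be stated, because no distribution of entry CGI is given. This review takes no position on which limit is right.

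**What to change.** 1. Reconcile the Sample text, both lists in Textbox 2 and the CGI Scale for Clinicians section into one non-overlapping CGI range. The clinical team sets the limits. If approved version 4 already has a single range, correct the article to match it.
2. Check the recorded entry CGI of everyone already enrolled against the reconciled range, and report any outside it as eligibility deviations.
3. State that no randomised child is removed from the primary analysis because of this ambiguity. This concerns the CGI criterion only. It leaves untouched the Study Population definition, which requires at least 10 sessions and is a separate matter.
4. Optionally, add one sensitivity analysis without the children outside the reconciled range.

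The cost is a short clarification, a check of scores that the preinclusion visit already collects, and possibly a few reported deviations. No change to the sample size is needed. If recruitment has ended, steps 2 to 4 can still be carried out.

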#### Randomization and Masking

To warrant clinical trial randomization, a random block sequence of 76 “1” (experimental) and 76 “2” (control) in 4 blocks of 38 numbers (19 “1” and 19 “2”) will be generated using the R program (R Foundation for Statistical Computing) by author [name] [33]. The sequence will be unknown to the recruiters [34].

In the preinclusion phase, patients will be informed about the research by the principal investigator (author [name]) and their suitability will be assessed according to the inclusion and exclusion criteria (Textbox 2). Subsequently, another author ([name]) will explain the research procedure in detail and summon the prerecruited participants. Once the consent form is signed, they will be randomly assigned by blocks using the electronic CRF with a ratio of 1:1. Randomization of the groups (MOON vs control) will be performed by the electronic CRF REDCap.

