## Results

The clinical trial is funded by the Community of Madrid (2020 Industrial Doctorates IND2020/BMD-17544). The expected date of data collection was between May 2023 and January 2024. The approximate completion date is March 2024. As of September 26, 2023, we have enrolled 62 participants. A total of 31 (20%) participants completed the study. The analysis of the total results is expected to be published in May 2024.

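### Arms are balanced within four randomisation blocks, but the stated ANOVA has no block term; adding one is a near-free gain in precision if SDQ change differs between blocks

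*Protocol article*

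**What the plan says.** Protocol article, Randomization and Masking: the list of 76 experimental and 76 control codes is generated "in 4 blocks of 38 numbers", each holding 19 of each code. The trial has one centre, and no stratification factor is named.

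Study Population (under Analyses): a 2-way ANOVA is specified "with time (pre and post) and group (experimental vs control) as factors and each measure as dependent variable". No block or period term appears. The Abstract adds only the t test and Mann-Whitney. The article does not say whether the ANOVA is of the repeated-measures kind.

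Primary End Point Analysis: the primary question rests on change in the parent-rated global SDQ from day 0 to the final visit.

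Sample Size Calculation: the plan assumes a "2-point mean drop (symptomatologic improvement) in the experimental group with a pooled SD of 4", and arrives at "approximately 152 participants with a diagnosis of ADHD", "taking into account a 15% dropout rate".

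Results: "The expected date of data collection was between May 2023 and January 2024"; 62 children had been enrolled by 26 September 2023.

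**The concern.** Forcing equal numbers per arm within a block removes differences between blocks from the comparison of arms. A model without block does not know this. It leaves those differences in the residual variance, so the standard error it reports is larger than the true sampling error of the arm contrast. The test then rejects too rarely, and some precision that the allocation has already secured is not used.

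It is reasonable to ask whether these blocks could differ. Each is a quarter of the trial. If children are allocated in order of enrolment, early and late blocks are followed over different parts of a window that runs from May to January, and so over different mixes of school and holiday. The SDQ includes hyperactivity and peer items, which might respond to that. School grades, taken from the report cards just before and just after treatment, are another measure for which calendar period could matter. All of this is plausible, but none of it is reported in the article.

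At stake is a modest amount of power for the primary SDQ comparison, and for the secondary measures analysed with the same model.

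**Working it through.** **Inputs from the article.** Difference 2, SD 4, 15% loss, 152 children (76 per arm), four blocks of 38. Significance: "The difference between the study groups will be considered significant when P<.05", taken as two-sided. SD 4 is taken as the SD of the analysed quantity; for a change score this corresponds, for example, to SD 4 at each visit with a pre-post correlation of 0.5.

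**Step 1: the plan's own figure.** An exact two-sample t test with standardised difference 2/4 = 0.5 needs 63.8, so 64 per arm. 64/0.85 = 75.3, so 76 per arm and 152 in total. The plan reproduces with no block term. Power is 86.5% with 76 per arm and 80.8% with 65 per arm (130 analysed, about 152 × 0.85).

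**Step 2: what omitting block does.** Assumption, not in the documents: block means of SDQ change vary with SD τ. Across four blocks, the expected variance between the block means (divisor 4) is 0.75τ². Hold the total variance at the planned 16, with losses spread evenly over arms and blocks:

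- Within-block variance: W = 16 − 0.75τ².
- True standard error of the arm contrast: √(4W/130).
- Standard error reported without block: √(4 × 16/130) = 0.702.
- Power without block ≈ Φ(2/SE_true − 1.979 × 0.702/SE_true), where 1.979 is the t critical value on 128 df.
- Power with block: noncentral t with SE_true and 125 df.

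For τ = 1: W = 15.25 and SE_true = 0.685. Without block, Φ(2.920 − 2.027) = Φ(0.893) = 0.814. With block, 0.826.

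| τ (points) | SE_true | Power without block | Power with block | Gain (percentage points) |
|---|---|---|---|---|
| 0 | 0.702 | 0.808 | 0.807 | about 0 |
| 0.5 | 0.698 | 0.810 | 0.812 | 0.2 |
| 1 | 0.685 | 0.814 | 0.826 | 1.2 |
| 1.5 | 0.664 | 0.822 | 0.849 | 2.7 |

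Without block, the null rejection rate, 2 × [1 − Φ(1.979 × 0.702/SE_true)], is about 4.3% at τ = 1 and 3.6% at τ = 1.5. It is below 5%, not above.

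**Step 3: level drift against drift in change.** Simulation of 152 children in four blocks of 38, 6,000 runs, within-block SD 4 at each visit, pre-post correlation 0.5, analysed on the change, with drift linear from first to last block:

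| Drift | SE without / with block | Power without / with block |
|---|---|---|
| Level, 2 points at both visits | 0.647 / 0.648 | 86.3% / 86.2% |
| Level, 4 points at both visits | 0.648 / 0.648 | 87.2% / 87.2% |
| Change, 2 points | 0.659 / 0.648 | 85.7% / 86.3% |
| Change, 4 points | 0.692 / 0.648 | 83.6% / 86.6% |

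Level drift cancels. Only drift in the amount of change matters. The 4-point case is extreme, at twice the planned effect. With no true difference, the model without block rejects in 4.6% (2-point) and 3.6% (4-point) of runs under drift in change.

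**Step 4: how long a block lasts.** From a May start to 26 September is 17 to 21 weeks. At 62 children, a block of 38 takes 38/(62/17) = 10.4 to 38/(62/21) = 12.9 weeks. Four such blocks take about 42 to 52 weeks, which does not fit a data-collection window of about 9 months that must also hold 90 days of follow-up. Enrolment over the remaining 6 months or so would give about 1.5 months per block. The article does not settle the length.

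**The case against.** The strongest case against is that nothing here is an error. Unstratified permuted blocks are often left out of the model, extra model terms are often left to a full analysis plan that is not shown, and the two passages do not contradict each other. The size also depends wholly on an assumed figure: at a between-block SD of 0.5 the gain is negligible, and the article never calls the blocks calendar periods. All of this stands, and it limits the point to an optional improvement. It does not remove it: the article does name its factors, block is not among them, and the suggested term costs almost nothing.

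Three stronger readings are tempting and should be set aside.

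- A reader might infer that power falls below the stated 80%. That happens only if block variance is added on top of the planned SD of 4. At τ = 1.5 the total SD becomes √(16 + 1.69) = 4.21 and power without block is about 78%. That describes a larger SD than the one planned. With the total held at 4, power without block stays at or above 80.8% across the table in Step 2.
- A reader might infer that any drift over recruitment harms the test. Drift in SDQ level common to both visits cancels if time-by-group is tested within participants. It would remain in the error only if pre and post were treated as independent observations, which the article neither says nor rules out.
- A reader might infer that each block matches a school term. The accrual arithmetic behind that fits poorly with the stated window, and neighbouring children on either side of a block boundary have nearly the same follow-up period.

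**Conclusion.** The point holds as a conditional gain in precision. The allocation is balanced within four blocks, the stated model omits them, and any difference between blocks in SDQ change goes into the error term and makes the test slightly conservative. For an assumed between-block SD in change of 0 to 1.5 points, the power forgone is about 0 to 3 percentage points at 130 analysed. This rests on the planned difference of 2 and SD of 4, even losses over arms and blocks, and a within-participant or change-score test. The documents report no difference between blocks, so the gain could be nil. There is no bias and no type I error inflation, and the sample size of 152 is sound without the term.

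**What to change.** Add one sentence to the analysis section: randomisation block (4 levels) is included in the primary SDQ model and in the secondary models, and the arms are compared within blocks. The form matters:

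- In a repeated-measures ANOVA, include block-by-time. A block main effect alone does not touch the within-participant error against which time-by-group is tested.
- In a change-score model, include block as a factor.

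Stating in the same sentence that time-by-group is tested within participants would also settle how level drift is handled.

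The cost is 3 degrees of freedom, with power moving from 80.8% to 80.7% at 130 analysed if blocks do not differ. The block follows from the allocation list, so no new data are needed and the sample size need not change.
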